# A virtual-reality based intervention on thoughts of the future self to reduce negative affect, depression, and suicidal ideation: protocol for a feasibility and acceptability randomized controlled pilot trial (FutureU for Mental Health)

**DOI:** 10.1186/s40814-025-01709-2

**Published:** 2025-11-15

**Keywords:** Virtual reality (VR), Intervention, Depression, Suicidal ideation, Episodic future thinking, Future self

## Abstract

**Background:**

Thinking about the future in a clear and detailed way is critical to daily life, generating meaning, motivation, and well-being overall. In depression and suicidal ideation (SI), executive functioning deficits can make future-oriented thinking (FT) particularly effortful. Many interventions address the quality of future thinking in depression and SI but are limited by the thoughts that a person can generate on their own. Finding ways to intervene on FT that do not rely fully on the overburdened cognitive processes of a person experiencing depression or SI may improve the efficacy of these interventions. The present pilot RCT investigates the feasibility, acceptability, and proof of concept for a novel virtual-reality (VR)-based intervention on thoughts of the future self (FutureU for Mental Health; FU-MH) to improve a person’s ability to think about the future and to reduce symptoms of depression and SI.

**Methods:**

Using a 4-month, randomized, controlled, participant-blind, add-on superiority trial with three parallel groups, we will evaluate the potential of a two-part VR-based intervention on thoughts of the future and the future self to reduce negative affect and depressive symptoms. We aim to recruit 60 participants and randomize them to either a control group, treatment group A, or treatment group B, where treatment groups are exactly the same with the exception of the order of presentation for intervention parts. Feasibility will be measured in terms of enrollment and retention, as well as subjective measures of participant engagement and embodiment in VR. Acceptability will be measured through participant self-report. Proof of concept will be evaluated through the demonstration of the intended effect on targeted cognitive mechanisms, evidence of improvement in clinical outcomes, and evidence of efficacy among those with cognitive processing deficits.

**Discussion:**

This study will provide valuable direction for further iterations of FutureU for Mental Health and a larger scale clinical trial. Implications of hypothesized outcomes include support for a novel intervention on thoughts of the future self in depression and SI, and VR as a novel medium of intervention and prevention in depression and SI.

**Trial registration:**

This trial was preregistered with OSF Registries prior to the beginning of any data collection on October 9, 2022 (doi: https://osf.io/8c5n6).

**Supplementary Information:**

The online version contains supplementary material available at 10.1186/s40814-025-01709-2.

## Background

“It is a peculiarity of man that he can only live by looking to the future–*sub specie aeternitatis*. And this is his salvation in the most difficult moments of his existence, although he sometimes has to force his mind to the task. […] The prisoner who had lost faith in the future—his future—was doomed.”—Viktor Frankl, *Man’s Search for Meaning.*

Science, philosophy, and lived experience all tell us that having faith in one’s future is critical to well-being, to meaning making, and to life itself. As Viktor Frankl describes, belief in the future is not always easy—“sometimes [one] has to force [their] mind to the task” [1]. This is especially true in depression and suicidal ideation where executive functioning deficits make future-oriented thought particularly effortful [2]. Many interventions address future thinking in depression and suicidal ideation but are limited by the thoughts that a person is able to generate on their own. Finding ways to intervene on future thinking that do not rely fully on the overburdened cognitive processes of a person experiencing depression or SI may improve the efficacy of these interventions. This is the focus of the present study, which aims to establish a proof of concept for a novel virtual reality-based intervention on thoughts of the future and the future self to reduce symptoms of depression and suicidal ideation. Virtual reality represents a promising and effective method for intervening on thoughts of the future [3, 4] but this use of VR has not yet been applied to depression and suicidal ideation.

Generating future thought involves a dynamic complex of cognitive processes which intersect with and are influenced by the cognitive processes impacted in depression [5]. Generation of detailed *positive* future thought requires attention, memory, cognitive flexibility, inhibition, and initiation. *All* of these processes are impacted in depression: attention and memory suffer from biases towards negative content [6, 7] and overgeneralization [8], thinking becomes more rigid [9], and inhibition [10] and initiation are more difficult [11].

According to the leading theory of future thought, episodic future thoughts are made up of elements of our episodic memory, flexibly recombined to create the novel imagined situation (constructive episodic simulation hypothesis [12]). For people experiencing depression, the building blocks of episodic future thoughts are overgeneralized, negative memories, and recombining these memories to generate a future thought requires a higher cognitive load than simply recalling them (see Fig. 1). Even when prompted, depressed individuals are less able to come up with positive possibilities, and any possibilities that they do generate are less vivid in their minds’ eye, which impacts the motivational power and believability of the thought [13–15]. Thus, while there are interventions, such as those cited above, that provide scaffolding for generating positive future thoughts, it is likely that the phenomenological experience of those thoughts is muted because it relies on cognitive resources that the person does not have access to.

**Fig. 1 Fig1:**
[figure not shown]
Future thinking in depression

## The potential utility of virtual reality

Virtual reality may provide a medium through which to activate the cognitive processes necessary to generate detailed, positive future thoughts. It may be possible that by scaffolding a person’s generation of a detailed, vivid, and positive experience of their own future through VR, they could “remember” (rather than flexibly generate) their future in a vivid and positive way, without having to rely too heavily on overburdened cognitive processes. The sensory-perceptual features of thought, such as vividness, visual details, sensory details, etc., are key to the feeling of pre-experiencing a moment [14]. These can be scaffolded and intensified by the visuals and sense of presence experienced by the person in VR in a way that traditional in-vivo methods are categorically unable to do. For instance, in VR, a person can embody and actually see themselves aged 20 years into the future, generating not only memories of the specific “future” moment during the VR exercise but also providing vivid, visual, and sensory building blocks of their future self from which to generate further future thoughts. Indeed, VR interventions focused on enhancing mental imagery have been found to deliver a stronger “dose” of the intended intervention effects than traditional in-vivo implementations, mediated by an increase in feelings of presence in VR and the vividness of the associated mental imagery [16, 17]. Figure 2 outlines our proposed model for how these advantages can play a role in more effectively intervening on depressive symptoms.

**Fig. 2 Fig2:**
[figure not shown]
Proposed model for future thinking assisted by virtual reality

## Introduction to FutureU for mental health

There are overlapping calls to action in the clinical field which seek interventions that leverage advancing virtual reality technology [18, 19], that address the future self and episodic future thinking [20], and that consider the experience of thoughts as relevant mechanisms for intervention alongside the content of thoughts [21, 22]. The virtual reality intervention proposed in this second study, FutureU for Mental Health, answers each of these calls. FutureU for Mental Health is comprised of three parts, two of which occur in virtual reality and are the novel aspect of this mental health intervention. Each part addresses a different function of future thinking. In this study, I assess its feasibility and acceptability and establish a proof of concept.

### Coping (safety) planning and reasons to live

In the first session, participants meet with the experimenter to develop a coping plan (or safety plan, if suicidal ideation is present) and to identify things that they are looking forward to in the future that make life worth living. This kind of plan, originally developed by Stanley & Brown [23], has been deemed a gold standard approach for suicide intervention and has been demonstrated to also be effective in helping people cope with other strong, difficult emotions that are not related to suicide [24]. This session is intended to help people develop a plan to anticipate a future moment where they may be struggling emotionally and to cope with it. This strategy is a key part of many empirically based therapeutic approaches, such as cognitive behavioral therapy and dialectical behavioral therapy.

Reasons life is worth living were asked to increase participants’ future orientation, which has been demonstrated to increase coping, particularly in the face of suicidal ideation and is commonly included as an addendum to the coping plan. Participants were asked to identify as many things as they could for 1 week, 1 year, and 5–10 years into the future.

Key to the assessment of the novel VR interventions, this plan and the reasons life is worth living inform the virtual reality interventions, which are intended to build upon the coping plan and to increase and enhance future thoughts around self-efficacy in coping with difficult emotions and the motivation towards positive future outcomes.

### Self-help intervention

The goal of the self-help intervention is to increase a person’s self-efficacy around coping with difficult emotions. In this intervention, participants will first embody an avatar of themselves as they are in the present day and will sit across the table from an avatar of themselves 1 week in the future, who is at that moment experiencing difficult emotions. Here, the future self avatar has a sad expression. Participants are then asked to use their coping skills to help their future self through the difficult moment. Participants are encouraged to reference their coping plan as needed. As coping statements are given, the future avatar’s mood is seen to visibly improve.

Next, participants are asked to time travel 1 week into the future to see life through the eyes of their 1-week older future self at the moment in time that they are struggling with difficult emotions. The participant then observes their future self in the mirror, an audio recording of their coping statements is played back, and they watch as their future self’s mood improves via facial expressions. This paradigm is based on an effective self-compassion intervention, which asked individuals to give compassion to a crying child and to then receive those compassionate statements themselves [25].

First and most basically, the practice of using the coping plan is expected to increase the participant’s perceived ability to leverage it in the future and to effectively cope with difficult emotions. Next, the vivid experience of watching the future self’s mood improve with coping statements both from the third- and first-person perspective is expected to increase the participant’s ability to see themselves in the future as a person capable of feeling better despite a difficult emotion. Importantly, we expect this experimental manipulation to affect the content of these thoughts—that they think about themselves getting past difficult periods in the future—and to also affect the quality of these thoughts, e.g., the thoughts are richer in imagery and emotional valence due to the sense of pre-experiencing that virtual reality affords. Further, mental imagery related to the self occurs often in both the first- and third-person perspective, so we anticipate that both giving and receiving coping statements will contribute to enhancing these thoughts.

After leaving the session, participants will be given a recording of their coping statements and asked to listen to them at least once before the next session in 1 week’s time. In addition, they are asked to reflect on what they learned from this VR experience. The repeated exposure to their coping statements and the active reflection on their self-help experience is expected to further increase their self-efficacy in managing difficult emotions, to help participants identify the value in thinking about themselves as capable of coping, and ultimately to improve coping itself.

Importantly, we included an intervention focused on the immediate future as the function of thoughts in the immediate versus the distal future is shown to differ. Thoughts of the immediate future are more directly related to motivation and action, and function as a way to guide a person through their day-to-day activities [26]. This may be especially relevant in the context of suicidal ideation where thoughts of the immediate future are of an inability to effectively cope with difficult emotions, in direct opposition to the intended outcome of this intervention.

### Positive future memories intervention

The goal of the positive future memories intervention is to increase a person’s ability to think richly and positively about themselves and the events that will happen to them in the future. In this intervention, participants will enter virtual reality and travel through time with the therapist (experimenter) 10 years into the future. In this future therapy space, the therapist and the participant will both have been age progressed to appear 10 years older. The age progression and the virtual future environment are key pieces of the experimental manipulation of the subjective elements of thoughts of the future because they provide participants with a sensorial experience of a “future” event.

The therapist will then walk the participant through a series of exercises aimed specifically at enhancing the participant's sense of themselves in the future, both in a physical and cognitive sense. This includes a set of embodiment exercises which require the participant to observe their 10-year older self in a virtual mirror. A higher sense of embodiment in virtual reality—a higher sense that it is really *them* in the virtual environment—increases the participant’s response to emotional stimuli presented in virtual reality [27]. This portion of the intervention also allows participants to not just observe their older selves but to reflect on what they see and create a narrative around who they are in 10 years’ time.

Then, the participant will be asked to tell the therapist about a positive memory of something that happened to them in the past 10 years (this is asked from the perspective of being 10 years in the future, so all events are future events that have not really happened). The event that they are asked about will be taken from their reasons why life is worth living exercise, which was completed in session 1. Participants will be asked to use as much detail as possible to describe the event and will be asked a series of prompting questions by the therapist to help enrich the level of detail given in the description. The recall task and prompting questions were taken from the Autobiographical Interviewing task, which was specifically designed to assess and increase the richness of autobiographical memories [28]. This task has been previously adapted for use in future thinking [29]. This task is intended to provide scaffolding for generating a detailed, rich positive future thought that is of importance to the participant. The guidance provided by the therapist, coupled with the vivid visual imagery of the person’s 10-year older future self, is expected to provide participants with a positive thought about their own future that is enhanced versus what they might be able to think about on their own. This is expected to occur by providing participants with concrete building blocks for thoughts of the future that do not need to be abstractly generated. For example, following the logic of the constructive episodic simulation hypothesis [12], to think about oneself in the future without the assistance of age progression technology, a person would have to flexibly generate that image by recombining images of themselves with images they hold of other older people or knowledge they have of how aging changes features. This requires a high cognitive load. This intervention may therefore allow for the activation of such vivid positive future thoughts in a way that circumvents some of the cognitive load prerequisites.

Thoughts of the distant future have been shown to function primarily for self-definition [26, 30]. Ten years in the future was chosen as the distance of travel for this intervention to provide flexibility in capturing events that were important and potentially self-defining to the individual participant. The event need not happen *in* 10 years but would have happened *by* 10 years.

Again, participants were given a recording of their detailed description of the future event and were asked to listen to it at least once prior to the next session in 1 week’s time. In addition, participants were provided with a photograph of their age-progressed future self. Participants were also again asked to reflect on what they could take away from this VR session. As with the self-help intervention, the repeated exposure to their detailed future thought, the image of their future self, and the active reflection on their positive future memory is expected to increase their ability to think in a vivid positive way about the future—in the case of suicidal ideation, to think of a positive future beyond suicide, to increase motivation towards future goals, and to ultimately improve coping.

## Study objectives

### Primary objective

The primary objective of this study is to determine whether the intervention is feasible to administer and acceptable to participants. This objective includes an assessment of whether the FutureU for Mental Health intervention was sufficient to establish a sense of realism, i.e., engagement with the virtual environment and embodiment of the virtual avatar.

### Secondary objectives

The key secondary objective of this study is to establish a proof of concept for the FutureU for Mental Health intervention. This will be established by (a) demonstration that the intervention has the intended effect on the targeted cognitive mechanisms (i.e. enhancement of the quality of mental imagery), and (b) evidence of improvement in clinical outcomes or reduction of negative affect versus the control group, both immediately following the intervention, and 1 week and 3 months post intervention.

Another secondary objective of this study is to assess whether the virtual reality intervention is strong for those participants who experience deficits in executive functioning.

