## Methods/design

### Study design and timeline

The intervention is designed as a randomized, controlled, participant-blind, add-on superiority trial with three parallel groups. Block randomization will occur with a 1:1 allocation. All participants will receive a Coping Plan intervention [24]. Participants only randomized to receive the Coping Plan will constitute the TAU control group. The TAU control design was chosen to ensure ethical responsiveness to the needs of all participants. Participants in each of the two treatment arms will additionally receive the FutureU-MH intervention. As the intervention is administered via two sessions each targeting different elements of the future self, treatment groups will follow an AB/BA design to allow for differentiation of session effects.

Participants will be assessed at 5 time points: pre-intervention (prior to randomization and completion of the Coping Plan), post-Coping Plan, pre- and post- each intervention session, and at both 1-week and 3 months follow-up (see SPIRIT figure in Table 1). These methods were in accordance with the Declaration of Helsinki and approved by the Ethics Council of the Max-Planck Gesellschaft.

**Table 1 Tab1:** SPIRIT Figure for FutureU for Mental Health Trial

	Timepoint	− 1	0	t1	t2	**t3**	**f1**	**f2**	
Activity/assessment	Approx. time to complete	Screening and online consent	Baseline assessment	TAU: coping plan	Intervention P1 and pre-post assessments/or interim assessment 1 (Control)	Intervention P2 and pre-post assessments/or interim assessment 2 (Control)	1 week follow-up	3 month follow-up	End of study
Enrollment:									
Pre-screening consent	1 min	X							
Screening	3 min	X							
Informed consent (online)	10 min	X							
Random allocation	N/A		X						
Interventions:									
Coping plan intervention (TAU)	25 min			X					
Self-help intervention (in VR)	30 min				E *or*	E *or*			
Positive future memories intervention (in VR)	30 min				E	E			
Assessments:									
Demographics	5 min		X						
Beck Depression Inventory—II	10 min		X					X	
C-SSRS	5 min		X		X	X	X	X	
Self-efficacy	3 min		X					X	
Self-reported future self and mood	10 min		X		X	X	X	X	
Prospective imagery task	5 min		X					X	
BRIEF-A	15 min		X						
Engagement/embodiment	3 min				E	E			
Feasibility outcomes	N/A								X
Acceptability, feasibility, appropriateness	3 min				E	E			
Intervention use	1 min					E	E	E	

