### Outcomes measures

All measures taken during in-lab sessions will be conducted on a laptop in the lab space. All measures taken during follow-up and online control sessions will be self-administered by participants via link to a Qualtrics survey.

*Primary objective measures—feasibility and acceptability of the intervention*
Feasibility: Number of eligible participants, willingness of participants to fully participate
(i)Rates of recruitment into the studyNumber of potentially eligible participants on SONA systems.Number of participants who completed the PHQ-9 screener and BDI-II item.Number (and proportion) of participants who were eligible to participate.Number (and proportion) of participants who were ineligible to participate at screening and why.Number (and proportion) of participants who consented to participate in intervention.Number (and proportion) of participants who scheduled the first in-lab session.Number (and proportion) of participants who completed the first in-lab session.(ii)Retention to treatmentNumber (and proportion) of participants who successfully completed all parts of the intervention (sessions 1, 2, and 3).Number (and proportion) of participants who drop out of the study and, when freely shared, reasons for drop out. In accordance with our informed consent, participants are free to drop out of the study at any point without explanation.(iii)Completion of between session tasks(iv)Number (and proportion) of participants who report needing to use their Coping Plan.(v)Number (and proportion) of participants who report using their Coping Plan when needed.(vi)Number (and proportion) of participants who report listening to their Self-Help recording in the week following the intervention session and 3 months following the intervention session.(vii)Number (and proportion) of participants who report listening to their Positive Future Memories recording in the week following the intervention session and 3 months following the intervention session.(viii)Attrition at post-treatment follow-up pointsNumber (and proportion) of participants who complete the 1-week follow-up questionnaire.Number (and proportion) of participants who complete the 1-month follow-up questionnaire.(ix)Levels of missing clinical outcome dataProportion of data completion for each questionnaire at each time-point.

Feasibility: Adherence/Compliance rates—Rating and adherence to intervention protocol. See above for details.

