(i)Improvement in symptoms of depression—Participants will respond to the Beck Depression Inventory—II (BDI-II) at baseline and at the 3-month follow-up session [48]. The BDI-II is the most widely used measure of depressive symptoms and has demonstrated good reliability and validity in clinical and nonclinical German samples [49]. The scale is comprised of 21 items assessing the presence and severity of depressive symptoms. Each item includes 4 response options ranging from no experience of symptoms to severe experience of symptoms; for example, 0 – *I do not feel sad* to 3 – *I am so sad or unhappy that I can’t stand it*. Scores are obtained by summing total items and range from 0 to 63. Total scores from 0 to 13 indicate minimal depression, 14 to 19 mild depression, 20 to 28 moderate depression, and 29 to 63 severe depression.Improvement in reported symptoms of depression among participants in the treatment condition from baseline to 3-months post-intervention follow-up.A larger improvement in reported symptoms of depression among participants in the treatment condition versus participants in the control condition from baseline to 3-months follow-up.(ii)Reduction in frequency and severity of suicidal ideation – Participants will respond to the German language validated Columbia – Suicide Severity Rating Scale adapted for use in Research [50] at baseline, each pre-intervention questionnaire, and the 1-week and 3-month follow-up. Based on responses, participant scores will be categorized as low, moderate, or high risk.Improvement in reported frequency and severity of suicidal ideation among participants in the treatment condition from baseline to each measurement occurring post-intervention (i.e., session 3 pre-intervention, 1-week follow up, 3-month follow up).A larger improvement in reported frequency and severity of suicidal ideation among participants in the treatment condition versus participants in the control condition from baseline to each measurement occurring post-intervention (i.e., session 3 pre-intervention, 1-week follow up, 3-month follow up).(iii)Reduction of negative affect, Improvement in Positive Affect—Participants will respond to the German language validated Positive and Negative Affect Scale (PANAS) at every measurement point [51]. The PANAS is made up of two 10-item scales measuring positive and negative affect. Each item is rated on a scale from 1 = Very Slightly, or Not at all to 5 = Extremely. Scores are obtained by averaging responses to items within the positive and negative subscales.Improvement in affect, i.e., increase in positive affect and decrease in negative affect, among participants in the treatment group from pre-to-post intervention and from baseline to 1-week and 3-month follow-up.A larger improvement in affect among participants in the treatment condition versus participants in the control condition from baseline to each measurement occurring post-intervention.(iv)Improvement in self-efficacy—Participants will respond to the German language validated General Self Efficacy Scale (GSES) at baseline and 3-month follow-up [52]. The scale has 10 items assessing participants’ overall sense of self-efficacy with dealing with difficulties. Items are rated on a scale from 1 = Completely Disagree to 4 = Completely Agree. Scores are obtained by averaging scores across all items.Improvement in self-efficacy among participants in the treatment condition from baseline to 3-month follow-up.A larger improvement in self-efficacy among participants in the treatment condition versus participants in the control condition from baseline to 3-month follow-up.

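### The promised comparison with control straight after the VR sessions is confounded by setting and timing, and no stated efficacy analysis uses the AB/BA order to separate the two sessions

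*Protocol article*

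**What the plan says.** **Objective.** The protocol article, under Secondary objectives, defines part of the proof of concept as "evidence of improvement in clinical outcomes or reduction of negative affect versus the control group, both immediately following the intervention", and again at 1 week and 3 months.

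**Targets.** Under Outcomes measures, affect has two. One is change within treatment only, "among participants in the treatment group from pre-to-post intervention and from baseline to 1-week and 3-month follow-up". The other is between arms: "A larger improvement in affect among participants in the treatment condition versus participants in the control condition from baseline to each measurement occurring post-intervention". The future-self scales carry the same pair of targets.

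**Schedule.** In Table 1 (Study design and timeline) the t2 column is headed "Intervention P1 and pre-post assessments/or interim assessment 1 (Control)" and the t3 column "Intervention P2 and pre-post assessments/or interim assessment 2 (Control)". The BDI-II is taken at baseline and 3 months. The C-SSRS is taken at baseline, before sessions, and at both follow-ups.

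**Mode.** Outcomes measures states: "All measures taken during in-lab sessions will be conducted on a laptop in the lab space". The next sentence states: "All measures taken during follow-up and online control sessions will be self-administered by participants via link to a Qualtrics survey".

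**Session order.** Study design and timeline says that "treatment groups will follow an AB/BA design to allow for differentiation of session effects". The secondary-objective part of Analyses describes its between-group comparisons (t-tests and latent growth curves) as treatment against control.

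**The concern.** A comparison with control straight after a session needs control ratings taken under similar conditions. Here the treated rating follows a VR session and is made in the lab. The nearest control rating is made online and is tied to no session. Any effect of place, or of being asked just after an engaging activity, falls on one arm only and adds to the apparent treatment effect. Momentary affect is the outcome most exposed to this. The pilot is meant to guide a full trial, so an inflated early effect could be carried into its design.

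The second issue is smaller. Participants are randomised to session order for a stated reason, but no efficacy analysis described in the article uses that randomisation.

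**Working it through.** The article gives no calculation for this point. Its numbers are consistent: 60/3 = 20 per group and 2 × 20 = 40 receiving the intervention.

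**1. What each arm provides at each time (affect and future-self scales)**

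| Time | Treated (A and B) | Control | Mode the same? |
|---|---|---|---|
| Baseline | lab | lab | yes |
| t2 | lab, before and after VR | online interim assessment | no |
| t3 | lab, before and after VR | online interim assessment | no |
| 1 week | online | online | yes |
| 3 months | online | online | yes |

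Counting from Table 1, a treated participant gives 1 + 2 + 2 + 1 + 1 = 7 affect ratings and a control gives 1 + 1 + 1 + 1 + 1 = 5. One control rating per interim assessment is inferred from the singular column label. The text of Study design and timeline also lists an assessment after the Coping Plan. If affect is rated there too, the counts are 8 and 6, and the gap of two remains.

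At t2 and t3 the controls (20 of 60) have moved from lab to online since baseline, while treated participants have not. By the follow-ups all three groups have made that move, so a shift due to mode is common to the arms in a change-from-baseline contrast.

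**2. Outcomes with no immediate value.** Neither the BDI-II nor the C-SSRS is taken after a session in any arm. The immediate part of the objective can therefore rest only on affect and the future-self ratings.

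**3. Possible size of the bias.** Let *m* be the shift, in SD units and favouring treatment, that comes from setting and timing. The contrast then estimates the true effect plus *m*. The documents give no value, so 0 to 0.5 SD is assumed, with no true effect, a two-sided 5% test and a normal approximation.

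- SE = √(1/40 + 1/20) = 0.274 SD
- Chance of a significant result favouring treatment = P(Z > 1.96 − *m*/0.274)

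| *m* (SD) | Chance |
|---|---|
| 0 | 2.5% |
| 0.2 | 11% |
| 0.3 | 19% |
| 0.5 | 45% |

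**4. Session effects.** At t2, group A has had only the self-help session (SH) and group B only positive future memories (PFM). Pooling returns the average of the two first-session effects; A minus B returns their difference. With illustrative values:

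| SH, PFM (SD) | Pooled | A − B |
|---|---|---|
| 0.4, 0.4 | 0.4 | 0 |
| 0.6, 0.2 | 0.4 | 0.4 |
| 0.8, 0 | 0.4 | 0.8 |
| 0, 0.8 | 0.4 | −0.8 |

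The pooled comparison cannot tell these cases apart, but the scheduled data can. A v B is randomised, matched on setting and timing, and free of carry-over both after the t2 session and just before session 3. Its unadjusted 95% half-width at 20 v 20 is t(0.975, 38) × √(2/20) = 2.024 × 0.316 = 0.64 SD. After session 3 starts, carry-over is expected: participants are asked to replay recordings and reflect between sessions, and the hypotheses have effects growing over time.

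**The case against.** **Wording of the targets.** The article already separates within-treatment pre-to-post change from between-arm change. For the C-SSRS it lists the post-intervention measurements, and the first is the rating before session 3, not one just after VR. For affect no such list is given, so a contrast using the post-session rating is a possible reading of the target and not a stated one. This has force for the outcome definitions. It does not help the objective itself, which names the immediate time point and the control group together. The pre-session t2 and t3 ratings also differ in mode between arms.

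**Exploratory status.** The primary objective is feasibility and acceptability, the efficacy analyses are described as exploring trends, and effects are expected to be strongest at the follow-ups. This limits the severity. It is an answer to imprecision, though, and not to bias.

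**Session effects.** Feasibility and acceptability are summarised by session, and a condensed article may leave an A v B efficacy contrast to a fuller plan. This stands, and makes the AB/BA point the weaker of the two.

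**Stronger readings that the document does not support.** A reader might infer that the immediate effect cannot be estimated at all. It can be computed from the common baseline, though with bias. A reader might infer that the therapist sits with treated participants while they answer, or that controls answer at home; neither is stated. A reader might also infer that pooling destroys the session comparison. It does not, because A v B remains estimable from data already scheduled.

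**Conclusion.** The point holds within limits. The versus-control objective at the immediate time point is not matched by the assessment schedule. For affect and the future-self scales the contrast is computable but confounded by setting and timing; for the BDI-II and C-SSRS there is no immediate measurement. The 1-week and 3-month contrasts are not touched.

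The size of the bias is unknown. The 11% to 45% range depends wholly on an assumed shift of 0.2 to 0.5 SD in favour of treatment, and a shift the other way would hide an effect. That controls give no before/after pair is inferred from the Table 1 labels.

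On AB/BA, the stated purpose has no matching efficacy analysis in the article, although the data would allow one with wide intervals. Severity is minor to moderate: this is an exploratory secondary objective of a pilot, and nothing in the progression criteria uses affect or a session contrast.

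**What to change.** 1. Remove the immediate time point from the versus-control objective. Report post-session change in affect and the future-self scales as within-arm description only.
2. Base between-arm claims on the 1-week and 3-month assessments, which all arms complete online (3 months only for the BDI-II). If any between-arm comparison at t2 or t3 is shown, including the C-SSRS before session 3, label it as confounded by mode and timing.
3. Do not move only the treated participants' pre-session ratings online. That would align them with controls but put a change of mode inside the planned within-arm pre-to-post comparison.
4. Either name the randomised A v B contrast from the first-session period (after the t2 session or before session 3), adjusted for baseline and given with its 95% CI, and treat second-session effects as descriptive; or withdraw the stated purpose of the AB/BA order.

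The cost is a change of wording in the objective and analysis sections, with no new data collection. The downside is that the claim of an immediate controlled effect is given up.
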